### Blinding

This is a single-blinded, double-arm, parallel-group study design, where only the participants will be blinded to their group assignment (intervention or control). This approach minimizes the risk of performance bias among participants. Outcome assessors, data analysts, and other study personnels will not be blinded as it is an educational interventional study.

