**Methods:**

The study is a multicentric randomized controlled trial, which will be conducted across 4 phases in Udupi, Mysuru, and Shivamogga districts of Karnataka. Phase 1 features a cross-sectional study design of 175 farmers to evaluate their baseline knowledge, attitudes, and practices on usage of pesticides. Phase 2 employs semi-structured interviews with 20–30 farmers and 10–20 key stakeholders, including pesticide dealers, scientists from Farm Science Centers [Krishi Vigyan Kendra (KVK)], and joint directors of agriculture to explore pesticide handling approaches, challenges, and community-specific needs while handling pesticides. The findings from Phases 1 and 2 will help in development and validation of an intervention in the form of educational video in Phase 3 which will be piloted. Phase 4 involves implementing the validated intervention and conducting long-term follow-up to assess the impact and sustainability. Phase 4 will be a two-arm, single-blind, parallel-group randomized controlled trial, with villages randomized 1:1 into intervention and control groups. The intervention group will receive a 15–20-minute educational documentary in the local language, while the control group will receive no intervention. The outcomes will be evaluated based on changes in Knowledge, Attitudes, and Practices (KAP) scores, with assessments conducted immediately post intervention, at 6 months, and at 12 months from the date of intervention. These will be correlated with outcomes including quality of life and laboratory parameters.

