### Study setting

The study will be conducted in 4 different phases. After a thorough literature review, it was evident that pesticide exposure and residue contamination were particularly high in certain regions of Karnataka. Data on pesticide exposure frequency were gathered from Farmer Producer Organizations (FPOs), which further supported the identification of high-risk areas. Additionally, factors such as crop diversification and regional agricultural practices were considered for study site selection. Based on these evidences, three districts—(a) Udupi, (b) Mysuru, and (c) Shivamogga— [31, 35, 36] were selected as the primary study sites. These districts have been reported to experience significant pesticide use, improper handling practices, and contamination risks in food and water systems. Prior studies have highlighted their vulnerability to pesticide-related health hazards, justifying their selection for this study. Furthermore, importance was given to interior villages within these districts to minimize contamination from external factors and focus on the specific challenges faced by the target group [31, 35, 36].

As a result, three districts that comprise various taluks were identified. Importance was given to interior villages in these taluks in order to minimize contamination and keep the study’s focus on the particular obstacles faced by the target group.

In-person field visits for data collection and laboratory investigations in these regions will be carried out. Additionally, permissions and ethical clearances from the appropriate authorities have already been obtained. In accordance with ethical guidelines, all participants will get a clear Participant Information Sheet (PIS) and Informed Consent (IC) form before enrolling to the study. The study complies with WHO and CONSORT 2025 guidelines and is registered with the Clinical Trials Registry India [CTRI] [37] with the registration number CTRI/2024/06/069678. The trial was registered on 28/06/2024 with the reference url https://ctri.nic.in/Clinicaltrials/regtrial.php? modid=1&compid=19&EncHid=55173.32324.

The study follows the SPIRIT 2025 guidelines [38] to ensure transparency and standardization. Details are provided in the supplementary file 1. Additionally, The SPIRIT 2025 figure format has been presented in Fig. 2 to illustrate the participant timeline and study procedures.

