### Intervention

The primary component of the intervention will be a 15–20-minutes educational documentary in the local language. Topics like safe pesticide usage, proper storage, disposal methods, and associated health risks will be covered in this documentary. These elements will be presented through a story that will be displayed as a short documentary or movie among the farmers. Cluster sampling method will be utilised for selecting participants based on characteristics including age, education, and years of experience with pesticides or agriculture. The intervention will be provided in the intended villages at community centres or village halls.

The control group will not receive any educational intervention during the study period. Participation records will be maintained to track adherence to intervention, and any participant’s decision to withdraw from the study will be documented. If withdrawn, data collected up to the point of withdrawal will be retained for analysis. The appropriate reason will be documented for withdrawal if available.

To maintain the integrity of the study, participants will be requested to refrain from engaging in other pesticide-related educational initiatives, although they may continue their regular farming activities. Adherence to the intervention and pesticide practices will be monitored through regular follow-up calls, personal visits, and collaboration with field officers, community leaders, and local organizations.

The detailed participant timeline has been provided in Fig. 2, following the SPIRIT 2025 format [39] .

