### Secondary outcomes

The secondary outcomes of this trial include (i) adherence to safe pesticide handling practices, (ii) knowledge on first aid for unintentional or occupational pesticide exposure. Additional outcomes comprise (iii) frequency of direct pesticide exposure, assessed through self-reported practices and associated health hazards during follow-up, and (iv) development and dissemination of a localized educational tool, evaluated qualitatively, to promote sustainable knowledge and practices. These outcomes have been selected for their clinical relevance in addressing the short- and long-term health risks associated with indiscriminate pesticide usage, enhancing overall safety, and fostering effective behavioural change among farmers. These outcomes will be assessed by an investigator through observation of the practices and using the self-reported checklists.

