In phase 4, the same villages from Phase 1 will be selected for recruitment. The districts will be randomized into control and intervention groups. Farmers will be identified using cluster sampling, with stratification based on age and agricultural experience. The intervention will be delivered to the experimental group at village halls or community centres. The cluster sampling approach ensures that participants are diverse in terms of age, educational level, and years of experience in agriculture allowing for a balanced representation across the groups.

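### The claim that participants are blinded, and that this limits performance bias, is not credible for a film-versus-nothing comparison, and the reason given for unmasked staff does not cover data analysts

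*Protocol article*

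**What the plan says.** The Blinding section makes three statements:

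- **Who is blinded.** The design is one "where only the participants will be blinded to their group assignment (intervention or control").
- **What this achieves.** "This approach minimizes the risk of performance bias among participants".
- **Who is not blinded, and why.** "Outcome assessors, data analysts, and other study personnels will not be blinded as it is an educational interventional study".

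The single-blind label also appears in the Methods part of the Abstract and under Trial design.

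The arms are defined elsewhere. The Abstract states: "The intervention group will receive a 15–20-minute educational documentary in the local language, while the control group will receive no intervention". The Intervention section confirms the comparator: "The control group will not receive any educational intervention during the study period". Recruitment of participants gives the setting: "The intervention will be delivered to the experimental group at village halls or community centres".

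The two primary outcomes are the KAP score and the SF-36 score, both from questionnaires (Primary outcomes). Under Data collection and management, Phase 4 data collection mirrors Phase 1, which is face to face. For the secondary outcomes: "These outcomes will be assessed by an investigator through observation of the practices and using the self-reported checklists".

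**The concern.** Blinding to assignment means that a participant cannot tell which arm he or she is in. With a film in one arm and nothing in the other, that normally needs a sham film, an attention control or some planned concealment. None is described, so the protocol asserts a property that its own arms do not provide.

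The reason for leaving everyone else unmasked is also misplaced. An educational intervention explains why those who receive or deliver it cannot be masked. It does not explain why the person analysing the data must know which arm is which.

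The outcomes are of a kind that masking helps to protect. A farmer who has just been taught safe practice may report safer practice than he or she follows, and an investigator who knows the village's arm may rate what is observed more kindly. Both errors would favour the film. A larger sample would not remove them. Yet the trial report would carry a single-blind label and a statement that performance bias had been minimised.

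**Working it through.** No stated figure depends on blinding, so there is nothing to recompute. The check sets the sections side by side.

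1. **Is the film arm blinded to assignment?** Its members attend a 15–20-minute showing in a village hall or community centre. They know that they received an educational film on pesticide safety. Nothing in the document hides this or gives the other arm something that resembles it.

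2. **Is the control arm blinded?** Possibly in part. Whole communities are allocated: villages according to the section on random sequence generation, districts according to Recruitment of participants. Control farmers in a separate village may never hear of the film. The protocol describes no step to bring this about, however, and some of what it does describe works against it. Under Study setting, "all participants will get a clear Participant Information Sheet (PIS) and Informed Consent (IC) form before enrolling to the study". The Intervention section also asks participants to avoid other pesticide-related education, which hints at what is being tested.

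3. **Does the stated reason cover each unmasked group?**
   - Staff who show the film: yes, they must know.
   - Outcome assessors: only in part. They could be kept from the allocation list, but the respondent or the venue may reveal it.
   - Data analysts: no. Data collection and management already says that all data will be coded, so a coded arm variable is a small addition.

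4. **Which outcomes are exposed?**
   - KAP and SF-36 (primary): questionnaire answers given face to face. Reported practice and attitudes are more open to desirable answering than knowledge items are.
   - Secondary outcomes: investigator observation and self-reported checklists, so open to both observer and response bias. The observation point applies to these only.
   - Laboratory parameters: less exposed, but the Primary outcomes section uses them as correlates and not as primary outcomes.

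5. **Can the bias be sized?** No. The document gives a KAP standard deviation of 10.33 from an earlier study, but no expected difference for Phase 4 and nothing on how far answers or ratings might shift. Any percentage would rest on two invented inputs.

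**The case against.** The strongest reply has four parts.

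- **Participants may be unaware of the comparison.** In interior villages chosen to limit contamination, farmers could know what they received without knowing that another arm exists. The content of the Phase 4 information sheet is not shown; the fuller description of a sheet belongs to Phase 1 recruitment. This stands as far as it goes. A reader might infer that participant blinding is impossible in this trial, and the document does not support that for control villages. But the Blinding section claims blinding to assignment itself, for all participants, and describes nothing that would deliver it.

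- **The unmasked staff are disclosed.** The protocol claims only less performance bias among participants and says openly that assessors and analysts are not blinded. That is correct: it is not a concealed defect, and a reader should not infer that protection against assessor bias was claimed and then withheld. What remains is that the stated reason does not reach the analysts.

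- **Assessors may not be maskable.** There are six villages, shared venues, face-to-face interviews, and adherence follow-up through visits and community leaders. An interviewer would often learn the arm. No team size is given, so it is not known whether different people could run the film and do the assessments. This stands and limits the remedy to what the team can do. Analysts may also guess the film arm from post-intervention scores, which weakens coded labels without making them useless.

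- **The harm is unquantified.** This is also true. A reader might be tempted to express the bias as a share of the treatment effect, but the document supplies neither figure needed.

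**Conclusion.** The point holds as an error of description together with one unjustified choice. The participant-blinding and performance-bias statements are not credible as written, because the arms are a film and nothing, with no sham, attention control or concealment described. The reason given for unmasked personnel does not justify unmasked data analysts. This is not a detail left to an analysis plan: the protocol states the property, the benefit and the reason.

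The direction of any bias would probably favour the film, given self-reported primary outcomes and partly observed secondary outcomes. Its size cannot be estimated from the document. The conclusion assumes that no concealment procedure exists outside the published text. If one does, it should be described, and the blinding claim limited to what that procedure achieves.

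The trial can still run. What is at stake is an accurate account of its protection against bias, and a cheap safeguard that is being passed over.

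**What to change.** 1. In the Blinding section, remove the statements that participants are blinded and that performance bias is thereby minimised. Describe the trial as open-label for participants, and correct the single-blind label in the Abstract and under Trial design.
2. Give the analyst a dataset with arms labelled A and B, and release the key only once the analysis is locked. Village and district names and film attendance records should stay out of that dataset until then, since with six villages either would reveal the arm.
3. Where the existing team allows, have the KAP and SF-36 interviews and the practice observation in each village done by members who did not run the screening there and do not hold the allocation list. State that this masking will be partial.
4. Report as a limitation that the primary outcomes are self-reported, and the secondary outcomes partly investigator-observed, under open conditions.

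Items 1 and 4 cost only wording, and item 2 a coded variable and a key held by someone else. Item 3 may cost nothing or may need extra staff; the document gives no team size, so it should be adopted as far as feasible. The described blinding status becomes less favourable, but it would then match the design.

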## Methods: data collection, management, and analysis

### Data collection and management

In phase 1, data will be collected in person through face-to-face interactions using baseline questionnaires, including the KAP questionnaire and the SF-36 Quality of Life (QoL) questionnaire from RAND Health. Additionally, qualitative interviews will be conducted, and laboratory tests (blood samples) will be collected from enrolled participants. All quantitative data will be stored in OpenEpi version 3.1 software and later transferred to SPSS version 20.0 (IBM, New York, NY, USA) for statistical analysis.

In phase 2, qualitative interviews will be recorded with prior consent, transcribed, and stored securely on a password-protected device. These recordings will be transcribed and translated to verbatim, and themes and sub-themes will be developed using NVivo software for qualitative analysis.

In phase 3, after developing the educational documentary, its validation will be conducted using a Likert scale (ranging from 1 to 4) and face-to-face focus group discussions (FGDs). These discussions will be recorded, transcribed, translated, and analysed to extract themes and suggestions, which will be incorporated to refine the documentary.

In phase 4, pre- and post-intervention questionnaires will be administered to both the intervention and control groups, mirroring the data collection process from Phase 1. The collected data will be stored in OpenEpi version 3.1 software and subsequently analysed using SPSS version 20.0 (IBM, New York, NY, USA).

Throughout the study, participant identities will remain anonymized, and all data will be coded for confidentiality. At the conclusion of the study, data will be discarded as per study protocols. Missing data, such as those resulting from loss to follow-up or participant withdrawal, will be documented with appropriate justifications and reported in the results.

### Statistical analysis

All data collected through the KAP and QoL questionnaires will be entered into SPSS version 20.0 (IBM, New York, NY, USA) for statistical analysis. Paired t-tests will be performed for continuous variables to compare pre- and post-intervention results. For improvements in quality of life and changes in laboratory parameters, the Wilcoxon Signed Ranks Test will be used. The results from the KAP surveys will be presented as mean ± standard deviation (SD). Qualitative interview data will be analysed using NVivo software, with thematic analysis to identify key patterns, insights and to understand the needs and perception of the farmers. Subgroup analyses based on confounding factors such as age, gender, and education level will be conducted to assess differential effects of the intervention. An intention-to-treat analysis will be performed and per-protocol analysis for participants deviating from the protocol.

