### Trial design

This study adopts a multi-phase, mixed-methods approach to address pesticide safety practices among farmers in Karnataka state. The study will be conducted in 4 different phases. Phase 1 is an analytical cross-sectional study, designed to evaluate the baseline knowledge, attitudes, and practices (KAP) of farmers using structured questionnaires. Phase 2 involves qualitative face-to-face interviews to gain deeper insights into the behavioural and contextual factors influencing pesticide usage and safety practices.

Phase 3 involves development and validation of need-based education module, where selection of experts will be carried out by purposive sampling technique. Phase 4 is a multicentric RCT, where 3 districts that includes 6 villages will be selected based on randomization. This study will be conducted as a two-arm, single-blind, parallel group with simple randomization of the districts and cluster randomization of farmers. The allocation ratio is 1:1, with one arm receiving the educational intervention and the other serving as a control group with no intervention. The outcomes will be assessed in terms of mean difference with the pre and post assessment in terms of KAP. The trial adopts a superiority framework [33] to assess the effectiveness of the educational intervention in improving pesticide safety knowledge, attitudes, and practices among farmers.

The below Fig. 1 depicts the trial process from recruitment to randomisation.

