### Primary outcomes

The primary outcomes of the trial are (i) Knowledge, Attitude, and Practice (KAP) scores, assessed using a validated KAP questionnaire, and (ii) Quality of Life (QoL) scores, evaluated using the SF-36 Questionnaire. Both outcomes will be measured at baseline, post-intervention, and periodic follow-ups, with results analysed as mean changes over time and correlated with laboratory findings to provide a comprehensive understanding of the intervention’s impact.

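### The named analyses for the RCT are all within-subject pre/post tests, and no comparison of intervention with control is specified

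*Protocol article*

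**What the plan says.** **Design.** Under Trial design: "The trial adopts a superiority framework". Also: "The allocation ratio is 1:1, with one arm receiving the educational intervention and the other serving as a control group with no intervention". The same section names 6 villages in 3 districts.

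**Outcome contrast.** Trial design adds: "The outcomes will be assessed in terms of mean difference with the pre and post assessment in terms of KAP". Primary outcomes lists KAP and SF-36 scores, "with results analysed as mean changes over time and correlated with laboratory findings".

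**Data.** Data collection and management says that in Phase 4 "pre- and post-intervention questionnaires will be administered to both the intervention and control groups".

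**Tests.** Statistical analysis names two inferential tests. For continuous variables: "Paired t-tests will be performed for continuous variables to compare pre- and post-intervention results". Then: "For improvements in quality of life and changes in laboratory parameters, the Wilcoxon Signed Ranks Test will be used". It also plans subgroup analyses of differential effects, without naming a test, and says: "An intention-to-treat analysis will be performed and per-protocol analysis for participants deviating from the protocol".

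**Sample size.** The Phase 4 paragraph under Sample size bases the calculation on a pilot of 12 farmers and calls the formula one for a paired t-test. It prints neither an expected difference nor a resulting number of farmers.

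**The concern.** A paired t-test or signed-rank test asks whether scores moved from baseline. A superiority trial asks whether they moved more in one arm than in the other. A change within the intervention arm combines any effect of the film with everything else that happens between visits, such as answering the same questionnaire again, season and secular trend. Only the contrast with the control arm removes these. Running the paired test in each arm and noting that one is significant and the other is not does not supply that contrast.

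At stake is the third objective, the impact of the education on KAP and quality of life through a randomised trial. Followed literally, the named tests could declare an ineffective film effective.

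**Working it through.** **1. Which stated elements compare the arms?**

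| Place in the article | What is fixed | Compares arms? |
|---|---|---|
| Trial design | Superiority framework, two arms | Implied, no test |
| Trial design, outcome sentence | Pre/post mean difference | No |
| Primary outcomes | Mean changes over time | No |
| Sample size, Phase 4 | Paired t-test formula | No |
| Statistical analysis, continuous variables | Paired t-test | No |
| Statistical analysis, QoL and laboratory | Wilcoxon signed-rank | No |
| Statistical analysis, subgroups and ITT | Effects and analysis populations | Implied, no test |

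**2. Is there a plan figure to reproduce?** No. Phase 4 has no printed sample size or expected difference. The 175 belongs to the Phase 1 survey and does not bear on this point.

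**3. How far can a common drift mislead the named test?**

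Inputs:
- KAP SD 10.33 (Sample size section).
- Two-sided alpha 5% (same section, through the 1.96).
- Assumed: 88 farmers per arm (half of 175, rounded up), because no Phase 4 figure is given.
- Assumed: pre-post correlation r = 0.5, with 0.3 and 0.7 as a range.
- Assumed: no film effect, the same drift in both arms, no clustering.

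Formulas, with drift d in SD units:
- SD of change = √(2(1 − r)); at r = 0.5 this is 1.
- Non-centrality of the paired t-test = d√n / √(2(1 − r)); at r = 0.5 and n = 88 this is 9.381 × d, with 87 degrees of freedom.

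| Drift (SD) | Drift (KAP points) | Non-centrality, r = 0.5 | P(significant), r = 0.5 | r = 0.3 | r = 0.7 |
|---|---|---|---|---|---|
| 0.05 | 0.5 | 0.47 | 8% | 7% | 9% |
| 0.10 | 1.0 | 0.94 | 15% | 12% | 22% |
| 0.20 | 2.1 | 1.88 | 46% | 35% | 67% |
| 0.30 | 3.1 | 2.81 | 79–80% | 65% | 95% |

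A two-sample t-test on the change scores has expectation d − d = 0 whatever the drift. Simulation at r = 0.5 gave a rejection rate of about 5% at all four drifts.

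**4. Does comparing the two paired p-values rescue it?** With independent arms, the chance of a significant result in the intervention arm and not in the control arm is p(1 − p). At a drift of 0.2 SD this is 0.458 × 0.542 = 0.248 (r = 0.5) or 0.668 × 0.332 = 0.222 (r = 0.7). Under a true null, roughly one trial in four or five would show the favourable pattern.

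**5. Would any mixed model do as the replacement?** No. With 3 villages against 3 and an assumed 29 farmers in each (6 × 29 = 174), a random-intercept model tested against the normal distribution rejects a true null in about 6%, 10% and 11% of trials at assumed intracluster correlations of 0.01, 0.05 and 0.10. A t-test on the six village means, with 6 − 2 = 4 degrees of freedom, stays at about 5%.

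**The case against.** **The article is a condensed document.** Detail may sit in a full protocol or analysis plan that is not shown. That would answer an omission. Here the article names its tests, and the design, outcome and sample size text points the same way. The objection does not remove the core.

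**A reader might infer that superiority will never be tested, or that the control arm plays no role.** The document does not support this. It states a superiority framework, measures both arms, and plans intention-to-treat and subgroup analyses that presuppose a treatment contrast. What can be said is that no between-arm test is specified.

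**A reader might also infer that paired tests cannot use the retained data of withdrawn farmers.** That is too broad. The Abstract schedules assessments immediately after the intervention, at 6 months and at 12 months. A farmer who leaves after the first of these has a complete pair for that visit. Only farmers without the relevant follow-up score drop out, and a baseline-adjusted model of follow-up scores loses those with none as well. How missing scores are handled may properly be left to a fuller plan.

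**The size rests on assumptions.** This is fair. The 88 is borrowed from a survey, and neither the drift nor the correlation has a source in the article. The direction does not depend on them.

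**The per-protocol sentence may only be loose English.** Probably so. It is a minor wording point, and nothing above rests on it.

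**Conclusion.** The concern holds in this form: the article fixes within-subject pre/post tests for both primary outcomes and for the laboratory values, describes the Phase 4 sample size on the same basis, and specifies no comparison of the arms. That does not fit its own two-arm superiority design. The named tests, used alone, cannot answer the trial's main question.

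Under the stated assumptions, false declarations of benefit run from about 8% at a drift of 0.05 SD to about 80% at 0.3 SD, against a nominal 5%. These rates illustrate the mechanism and do not predict the trial. The qualitative conclusion needs only some change shared by both arms. It should be corrected before the Phase 4 analysis.

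**What to change.** 1. Make the RCT analysis a baseline-adjusted between-arm comparison of KAP and of SF-36 at a named time point. Report the arm difference with a 95% confidence interval and analyse farmers by randomised allocation. Use the same type of contrast for laboratory values, on a suitable scale if skewed.
2. Account for the unit of randomisation with a method valid for few clusters. Examples are a village-level analysis with t degrees of freedom based on the number of villages, or a mixed model with a Kenward-Roger type correction. The unit must first be settled: Random sequence generation and randomization says villages, whereas Recruitment of participants says districts.
3. Keep the paired t-test and the signed-rank test as description of within-arm change only.
4. Word the per-protocol set as excluding farmers who deviate from the protocol.
5. Restate the Phase 4 sample size and power on the same clustered between-arm contrast, giving the expected difference, the pre-post correlation and the intracluster correlation.

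**Cost.** No new data are needed for the analysis, since both arms are already measured at baseline and follow-up. It is more than a change of wording, because the sample size calculation must be redone. With about 6 villages the restated power is likely to be less favourable, which may raise the question of adding villages.
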